### Outcome measures

Arm function (impairment, activity and participation) will be assessed in
accordance with the ICF Classification of Functioning, Disability and Health [26]. All participants will be assessed at four time points: three days
prior to commencement of the intervention (baseline, 0 weeks), within one week
of completion of the intervention (post-intervention, 4 weeks), and following
completion of the intervention at 26 and 52 weeks. Assessors will be provided
with guidelines for administering the measures.

Demographic information about participants will be collected from their medical
record and will include age, gender, date of stroke onset, type (ischaemic or
haemorrhagic) and location (cortical, subcortical, cortical and subcortical or
brainstem) of stroke, stroke medical intervention (e.g. thrombolysis),
co-morbidities and medications.

#### Primary outcome measure

The primary outcome measure will be performance on the MAS item 6 at the post
intervention time period (4 weeks). The MAS is designed to measure recovery
of the affected limb over 3 task-related subscales (upper arm function, hand
and advanced hand movements) that are scored from 0–6. It is the
stroke recovery scale most commonly used in clinical practice in Australia
and takes less than 10 minutes to complete. The reliability and validity of
this measure with the stroke population has been previously documented [27]. It has been shown to be sensitive to change in performance in
people with severe upper limb disability after training with SMART Arm [16,19].

#### Secondary laboratory outcome measures

The functional force generating capacity of the impaired limb will be
assessed using a dynamic and an isometric reaching task similar to previous
protocols [16,17]. In both tasks, surface EMG activity will be collected from
triceps brachii lateral head, biceps brachii, anterior deltoid, upper
trapezius, external rotators, lower trapezius and serratus anterior. EMG
will be obtained using single differential pre-amplified (gain 1000)
parallel bar electrodes (Bagnoli, DELSYS, 8-channel System, Boston, MA, USA)
with a fixed inter-electrode distance of 10 mm and positioned according to
SENIAM guidelines [28]. A reference electrode will be attached over the bony prominence
of the seventh cervical spinous process. Signals will be sampled (1000Hz)
using a Power 1401 Data Acquisition System (Cambridge Electronics Design,
Cambridge, UK) and Spike2 software (version 6.02). Time series data will be
collected and stored using Spike2 and processed using custom routines in
Matlab (Mathworks Inc., Nattick, MA).

Participants will be seated at a custom-built apparatus with the upper limb
in a pendant position, the elbow flexed and the forearm and hand restrained
in pronation via a custom built brace. For all measures a computer monitor
positioned directly in front of the participant will provide visual feedback
on a vertical bar scale. In the dynamic task, the brace will be secured to a
manipulandum mounted on a linear slide restricting motion of the upper limb
to flexion/ extension of the shoulder and elbow. A potentiometer attached to
the slide will measure transducer, reaching, linear displacement. The upper
limb will be placed at a standardised starting position with the elbow at 90
degrees of flexion. Upon presentation of a tone, participants will be
required to ‘reach forward as far as possible’ in five separate
trials. In the isometric task, the participant will be required to push
forwards (elbow extension) in a position of 150 degrees of elbow flexion
against a manipulandum instrumented to measure force. In five separate
trials, following a tone, participants will be instructed to ‘push as
hard as possible’ and to keep pushing for five seconds. In both tasks
continuous visual feedback of the applied force will be provided along with
verbal encouragement. During each contraction, force or reach distance and
EMG recordings will be obtained. On the basis of these recordings, peak
force, distance, time to peak and the muscle onset times, amplitude
(root-mean-square (RMS)) and triceps to biceps ratio of EMG RMS amplitude
will be calculated.

In a subset of the participants, the collection of EMG signals will be
triggered and synchronized using an OptiTrack™ 6 camera 120 Hz system,
with Tracking Tools™ computer software (NaturalPoint, Inc, OR, USA)
which will collect kinematic data. Upper limb movement will be tracked via
the recording of reflective marker clusters placed on the
participants’ upper arm, distal forearm, sternum, and acromion and
acromioclavicular joints. Kinematic data for analysis will include
displacement, velocity and changes in angles of upper arm segments and
markers.

#### Secondary outcome measures: clinical

A range of clinical measures will be collected to measure the presence of
impairments post stroke. To measure strength, lateral head of triceps
brachii muscle power will be assessed using manual muscle testing according
to MRC ratings from 0–5 [29]. To measure the active range of movement of finger flexion and
extension, thumb extension and abduction, elbow flexion and extension and
shoulder abduction and adduction, assessment according to the protocol
described by Uswatte et al. [30] will be performed. To measure the presence of spasticity of
biceps brachii and resistance to passive elbow extension, the modified
Ashworth Scale [31] and Tardieu Scale [32] will be administered. To evaluate joint tenderness on passive
movement of the hemiplegic shoulder, the Ritchie Articular Index will be
administered [33,34]. To describe participants at baseline only, the Cognitive
Linguistic Quick Test [35] and Nottingham Sensory Assessment [36,37] will be administered. Motor Assessment Scale items 7 (hand
movements) and 8 (advanced hand activities) will be performed to monitor for
any carryover improvement in hand function. To examine upper limb function
at the participation level, two self-report measures will be used. The
Stroke Impact Scale will be used to measure the impact of the intervention
on the stroke survivor’s recovery [38]. The Motor Activity Log will be administered to all subjects to
rate how well and how much they use the paretic limb spontaneously in
everyday tasks [30].

### Data analysis

Data analysis will be performed on an intention-to-treat basis using an alpha
level of 0.05. Descriptive statistics will be used to ensure comparability of
scores between groups at baseline, to describe performance at each phase and to
test whether the assumptions for use of parametric statistics have been met. If
the assumptions for F or t-tests are violated, equivalent non-parametric
statistics will be utilized. The main hypothesis will be tested using mixed
effects models, in a 3 group (SMART Arm + OT stim, SMART Arm alone, usual
therapy) × 4 phase (0, 4, 26, 52 weeks) model. This will be followed by
between-groups planned comparisons. All secondary outcomes will be analysed in a
similar manner.

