### Sample size

The principle endpoint is post intervention (4 weeks). Our previous RCT
demonstrated that stroke survivors using the SMART Arm alone or with electrical
stimulation demonstrated significant improvements in MAS-6 scores compared to
the control group [16]. On this basis, we estimate a mean improvement of 1.8 (SD 2) in the
usual therapy group, 2.91 (SD 2) in the SMART Arm alone group and 3.91 (SD 2) in
the SMART Arm with OT-stim group. To achieve 80% power and a significance of
0.05 with pairwise comparisons, 22 subjects are required per group, to total 66
subjects. A 15% dropout rate will be allowed to account for withdrawals, thus 25
subjects will be recruited per group, totalling 75.

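### The primary model treats baseline MAS item 6 as an outcome phase and states no adjustment for it, so the 4-week contrast may give up precision that could be had at no cost

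*Protocol article*

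**What the plan says.** The Data analysis section of the protocol article names the primary model: a mixed effects model with three groups and all four assessment times as phases. The sentence that sets this out and leads on to the planned comparisons contains "therapy) × 4 phase (0, 4, 26, 52 weeks) model. This will be followed by". Week 0 is thus a level of the response. No covariate is named, and nothing says that the groups share a common mean at week 0. Outside the model, baseline appears only in a sentence on how alike the groups are at entry, which contains "level of 0.05. Descriptive statistics will be used to ensure comparability of".

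Two other sections bear on which 4-week contrast is meant. Under Primary outcome measure, the endpoint is the MAS item 6 score at 4 weeks. Under Sample size, the planning values are changes, introduced with "On this basis, we estimate a mean improvement of 1.8 (SD 2) in the". That figure is for usual therapy; the corresponding values are 2.91 for SMART Arm alone and 3.91 when OT-stim is added, each again with an SD of 2.

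Under Population, entry requires a MAS item 6 score of 3 or less, so baseline scores lie between 0 and 3. Under Randomisation and blinding, permuted blocks are used and no stratification factor is given. ANCOVA is listed under Abbreviations but is not used in the analysis text.

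**The concern.** On the ordinary reading of a group-by-phase model, each group has its own freely estimated mean at week 0. The between-group contrast at 4 weeks is then one of two things: the difference in 4-week means, or the difference in change from week 0. The first ignores the baseline score. The second subtracts it with a fixed coefficient of 1. A baseline-adjusted contrast estimates that coefficient from the data, and in large samples it has a variance no greater than either.

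With 25 randomised per group and no stratification stated, the groups can differ at baseline by chance. Descriptive statistics can show such a difference but cannot secure comparability. If the raw 4-week contrast is used, the difference passes into the treatment estimate. Precision matters here because two of the three pairwise contrasts are short of power on the article's own planning values.

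**Working it through.** **Inputs from the article.** Difference between SMART Arm alone and usual therapy: 2.91 − 1.8 = 1.11. SD of change: 2. Completers per group: 22. Significance level: 0.05, taken as two-sided. Baseline range: 0 to 3.

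**Inputs assumed, because the article does not give them.** Baseline SD s0 = 1.1. Correlation ρ between baseline and 4 weeks: 0.3, 0.5 and 0.7.

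**The plan's own figure.** The Sample size section claims 80% power at "0.05 with pairwise comparisons, 22 subjects are required per group, to total 66" in total. A two-sample t test with SD 2 and 22 per group gives 43.6% for the 1.11 difference, 36.7% for OT-stim against SMART Arm alone (3.91 − 2.91 = 1.00) and 92.8% for OT-stim against usual therapy (3.91 − 1.8 = 2.11). The stated power is reached for only one pair. That is a separate matter; 43.6% serves here as the change-score reference.

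**Formulas.**
- The 4-week SD s1 consistent with a change SD of 2 solves s0² + s1² − 2ρ·s0·s1 = 4, so s1 = ρ·s0 + √(ρ²·s0² + 4 − s0²).
- SD after baseline adjustment: s1·√(1 − ρ²).
- Variance ratio, adjusted to raw: 1 − ρ². It does not depend on s0.
- Variance ratio, adjusted to change: s1²(1 − ρ²)/4.

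**Worked at ρ = 0.5.** s1 = 0.55 + √(0.3025 + 4 − 1.21) = 0.55 + 1.759 = 2.309. Adjusted SD = 2.309 × √0.75 = 1.999. Ratio to change = 1.999²/4 = 0.999. Ratio to raw = 0.75.

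| ρ | 4-week SD | Adjusted SD | Cut against raw | Cut against change | Power raw | Power change | Power adjusted |
|---|---|---|---|---|---|---|---|
| 0.3 | 2.03 | 1.94 | 9% | 6% | 42% | 44% | 46% |
| 0.5 | 2.31 | 2.00 | 25% | 0% | 34% | 44% | 44% |
| 0.7 | 2.61 | 1.86 | 49% | 13% | 28% | 44% | 49% |

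Power is for the 1.11 difference with 22 per group (noncentral t), ignoring the one degree of freedom spent on the covariate.

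**Sensitivity to the assumed baseline SD.** For s0 of 0.5, 1.0 and 1.5 and the same correlations, the cut against change runs from 0.4% to 32%. The cut against raw stays at 9% to 49%.

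**Chance imbalance.** With 25 per group, the standard error of the baseline difference is 1.1 × √(2/25) = 0.31 points. At ρ = 0.5 the slope of 4-week score on baseline is 0.5 × 2.309/1.1 = 1.05. An imbalance of one standard error therefore shifts the raw contrast by 1.05 × 0.31 = 0.33 points, about 30% of 1.11. It shifts the change contrast by (1.05 − 1) × 0.31, or about 0.02 points.

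**The case against.** The strongest objection is that the plan does use baseline. A group-by-phase interaction compares change from week 0, and the sample size is planned on change. At ρ = 0.5 the change contrast already does almost everything adjustment would do. This stands: a reader might infer from the descriptive sentence that baseline is merely tabulated, and the model does not support that. What remains is that baseline is not stated to be a covariate or to have a common mean, and that the endpoint section points to the score rather than to change.

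A second objection is that free week-0 means are inferred from a one-sentence outline. With those means constrained equal, the same model would match the efficiency of baseline adjustment, and the full protocol or SAP may say so. ANCOVA in the abbreviation list is at most a weak hint that adjustment was considered. This limits the point to what the article states; it does not show that adjustment is ruled out.

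Two stronger readings are tempting and should be resisted:
- **Equal SDs at both visits.** The textbook ratio (1 + ρ)/2 would suggest variance cuts of 35%, 25% and 15% against change scores, and power for the 1.11 difference rising from 44% to 55% at ρ = 0.5. With a change SD of 2, equal SDs need a baseline SD of 2/√(2(1 − ρ)): 1.69, 2.00 and 2.58. Scores limited to 0 to 3 cannot have an SD above about 1.5, so these gains contradict the entry criterion.
- **Time since stroke.** The article collects it ("record and will include age, gender, date of stroke onset, type (ischaemic or" haemorrhagic) and names no analysis use. A reader might call that lost precision. The article gives no association with outcome, and further covariates such as this or site are commonly left to the full protocol or SAP. Neither is a finding.

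**Conclusion.** The point holds as a free improvement, not as an error that invalidates the analysis. As stated, the model puts baseline on the response side without adjustment or constraint and leaves open whether the 4-week comparison is of scores or of change.

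The size depends on that choice. If raw scores are compared, the variance given up is 9% to 49% for correlations of 0.3 to 0.7, and chance imbalance stays in the estimate. If change is compared, the loss is 0% to 13% at a baseline SD of 1.1 and may be negligible. All of this rests on assumed correlations, and the change-score figures also on the assumed baseline SD. The ρ = 0.7 row implies a 4-week SD of 2.61 on a 0 to 6 scale, whose largest possible SD is 3, so its power figures are at the edge of what is plausible.

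The efficiency claim is a large-sample one. In a simulation with 22 per group and equal SDs, estimating the slope raised the variance ratios slightly (0.666, 0.766 and 0.872 against 0.65, 0.75 and 0.85). Where the theoretical gain over change is nil, adjustment may therefore cost a little. Adjustment does not repair the power shortfall: adjusted power for the 1.11 difference is still about 44% to 49%.

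**What to change.** In the Data analysis section:
- Fit the mixed model to the 4-, 26- and 52-week scores with baseline MAS item 6 as a covariate interacting with visit. Alternatively, keep week 0 as a phase and constrain the group means to be equal there.
- Name the baseline-adjusted 4-week contrast as the primary comparison. This also settles the choice between score and change, because adjusting either one for baseline gives the same treatment contrast.
- Say that descriptive statistics *describe* baseline scores, in place of *ensure*.

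The cost is a change of wording. MAS item 6 is already measured at week 0, and neither the sample size nor the visits change.

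### The primary endpoint is MAS item 6 at 4 weeks, but the main hypothesis is assigned to a four-phase, 52-week model and the 4-week between-group contrast is not fixed as the deciding test

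*Protocol article*

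**What the plan says.** Three sections of the protocol article bear on the confirmatory question.

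- **Primary outcome measure:** "The primary outcome measure will be performance on the MAS item 6 at the post". The sentence goes on to identify that time point as 4 weeks.
- **Sample size:** "The principle endpoint is post intervention (4 weeks". The basis is introduced with "we estimate a mean improvement of 1.8 (SD 2) in the", where the figure of 1.8 belongs to usual therapy; SMART Arm alone has 2.91 and SMART Arm with OT-stim 3.91, each with SD 2. For 80% power the requirement is given as "0.05 with pairwise comparisons, 22 subjects are required per group, to total 66".
- **Data analysis:** "The main hypothesis will be tested using mixed". The three groups are crossed with the assessment phases, as in "therapy) × 4 phase (0, 4, 26, 52 weeks) model. This will be followed by". What comes next in that section is a set of comparisons between groups that are planned but not tied to a phase, and the secondary outcomes get the same treatment.

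The Data analysis section mentions 4 weeks only as one of the four phases. It does not say which term of the model decides the main hypothesis, or at which phase the planned comparisons are made.

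**The concern.** The endpoint and the sizing point to one question: do the groups differ in MAS item 6 at 4 weeks? The sentence that names the test of the main hypothesis points to a model covering a year, with the between-group comparisons placed after it.

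The overall tests that a group-by-phase model yields are these:

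- the group-by-phase interaction, with (3 − 1) × (4 − 1) = 6 df, which pools group differences in change at 4, 26 and 52 weeks;
- the group main effect, with 2 df, which averages over all four phases. These include baseline, where randomisation makes the true difference zero.

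Neither is the 4-week group difference. If one of them is read as the deciding test, the main hypothesis could be declared supported because of late differences alone. A real 4-week effect could also be missed under some later patterns. The same data could give different verdicts depending on which term the analyst takes as the test.

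**Working it through.** **Inputs from the article.** Mean improvements at 4 weeks are 1.8, 2.91 and 3.91, with SD 2 and 22 per group (Sample size). Alpha is 0.05 (Data analysis).

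**Assumptions, because the article gives no figures.** Tests are two-sided. The four phases have compound symmetry with correlation ρ from 0.3 to 0.7, scaled so that the SD of change is 2. Effects at 26 and 52 weeks are multiples of the 4-week effects.

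**The plan's own figure.** With two-sided 0.05 t-tests and 80% power, the three pairwise differences need:

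- 16 per group for 2.11 (OT-stim vs usual therapy);
- 52 per group for 1.11 (SMART Arm alone vs usual therapy);
- 64 per group for 1.00 (OT-stim vs SMART Arm alone).

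A one-way ANOVA at 4 weeks needs 19. None of these gives 22. That is a separate matter; 22 is used below as the stated size.

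**Reference: 2-df group test at 4 weeks.** The mean of the three improvements is 8.62/3 = 2.873. The deviations are −1.073, 0.037 and 1.037, with sum of squares 2.228. The noncentrality is 22 × 2.228 / 4 = 12.25. Power by noncentral chi-square is 0.89 (0.87 by noncentral F).

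**6-df interaction.** Under compound symmetry with change SD 2, the changes from baseline at 4, 26 and 52 weeks have covariance 2(I + J), where I is the identity and J the matrix of ones. The inverse is ½(I − J/4). For a pattern p = (p₄, p₂₆, p₅₂):

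q = ½[Σp² − (Σp)²/4], and noncentrality = 22 × 2.228 × q = 49.02 q.

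This does not depend on ρ.

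**2-df group main effect.** The variance of a subject's four-phase mean is v = [2/(1 − ρ)] × (1 + 3ρ)/4. It is 1.36, 2.50 and 5.17 for ρ = 0.3, 0.5 and 0.7. The noncentrality is 49.02 × (Σp/4)²/v.

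| Pattern (4, 26, 52 weeks) | q | Noncentrality, 6 df | Interaction | Main effect, ρ = 0.7 to 0.3 | 4-week test |
|---|---|---|---|---|---|
| Sustained (1, 1, 1) | 0.375 | 18.38 | 0.92 | 0.53 to 0.99 | 0.89 |
| Halves and stays (1, ½, ½) | 0.250 | 12.25 | 0.75 | 0.26 to 0.77 | 0.89 |
| Fades to zero by 52 weeks (1, ½, 0) | 0.344 | 16.85 | 0.89 | 0.16 to 0.51 | 0.89 |
| 4 weeks only (1, 0, 0) | 0.375 | 18.38 | 0.92 | 0.10 to 0.25 | 0.89 |
| Late only (0, 1, 1) | 0.500 | 24.51 | 0.98 | 0.26 to 0.77 | 0.05 |
| Late only, half size (0, ½, ½) | 0.125 | 6.13 | 0.41 | 0.10 to 0.25 | 0.05 |

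The last two rows show the overall tests rejecting when nothing differs at 4 weeks. The second row is the only one of the first four in which the interaction loses power against the 4-week test.

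**The case against.** A reader might infer that the deciding test does not test the primary endpoint at all. The article does not support that. It names a model, not an omnibus test; a group-by-phase model contains the 4-week between-group contrast; and the planned comparisons may be exactly that contrast. Read with the primary outcome and the pairwise sample size, 4 weeks is a natural reading of them. Nor does the text say that the comparisons depend on a significant overall test. All of this stands, and a four-phase mixed model is not wrong in itself.

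It is also fair to say that the power loss depends on the pattern. The interaction keeps 0.92 for a sustained effect, 0.92 for a 4-week-only effect and 0.89 for a fade to zero by 52 weeks. The 0.75 needs an effect that falls to half and stays there. The 0.98 needs no difference at 4 weeks and the full planned effect long after a four-week intervention; at half that size it is 0.41. The main effect is the less likely criterion in a design with a baseline phase. So a general claim that the overall test misses a fading effect would be wrong.

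A further argument is that naming the contrast is detail that an article leaves to a fuller document. That holds only in part. The article does more than stay silent: it assigns the main hypothesis to the 52-week model, with baseline as a phase, and puts comparisons at no named phase after it. Its own sections on outcome and sample size name a different time frame.

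**Conclusion.** The point holds in this form: the endpoint and the sizing are fixed at 4 weeks, while the stated test of the main hypothesis spans 0 to 52 weeks and does not fix the 4-week contrast as decisive. The overall tests are not interchangeable with that contrast. In the patterns examined, the interaction's rejection rate ranges from 0.75 to 0.92 when the planned 4-week effect is present, against 0.89 for the 4-week test. It reaches 0.98 when the 4-week effect is absent and the later effects are full. The main effect ranges from 0.10 to 0.99 when the 4-week effect is present.

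These figures rest on 22 per group, change SD 2, compound symmetry and assumed later effects. They show that the choice of term matters; they do not predict what the trial will find. The ambiguity bears on what counts as a positive trial, so it should be settled before unblinded analysis.

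**What to change.** State in Data analysis that the primary test is the baseline-adjusted between-group contrast, or contrasts, in MAS item 6 at 4 weeks. These are estimated from the mixed model, reported with 95% CI, and not conditional on the omnibus test. State also how alpha is shared if more than one pairwise contrast is primary. Make the 26- and 52-week contrasts and the overall group-by-phase test secondary.

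The cost is a change of wording: the data and the model family stay the same. The downside is that an effect emerging only after 4 weeks can be no more than a secondary result, which agrees with the stated endpoint. Naming the contrasts also shows their separate power at 22 per group (t-test, two-sided 0.05): 0.93 for OT-stim vs usual therapy, 0.44 for SMART Arm alone vs usual therapy, and 0.37 for OT-stim vs SMART Arm alone. The choice of primary contrast or contrasts should be made with these in view.
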